### Sample size

Sample size for the quantitative part is estimated at 25 staff members and 30 patients. For the qualitative part, sample size is estimated at 20 staff members and 20 patients who will be purposively selected by the researchers.

### Analysis

#### Quantitative data

Demographic data for participants will be presented as means and proportions. In the SSED research tradition, focus is on changes within subjects, not between groups [33]. Thus, traditional inferential statistics are rarely used. Visual and numerical methods will be used to analyse data from the SSED study [51]. Visual inspection of the data requires comparing levels, trends, and changes between intervention phases [33]. Also, the percentage of non-overlapping data statistics will be calculated, i.e. the percentage of phase B data that overlaps with the most extreme data point in phase A [33]. In this study, data from patients and staff will be analysed separately. Measurement data for each of the questionnaires will consist of the mean ratings from all participants, patients, and staff respectively, answering at each point in time.

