### Procedure

In the overall project, the evaluation will consist of two phases (A and B), and a follow-up, in line with the SSED. Baseline measures will be established during phase A, through outcomes measured twice a week for approximately 5 weeks. During these 5 weeks, staff and patients will not be introduced to the new environment. In phase B, staff and patients will be introduced to the new environment, and outcomes will be measured once a week over a period of 2 months.

The semi-structured focus group interviews with staff will be conducted at the end of phase B while patients will be interviewed individually very near to their discharge from the ward during phase B. Follow-up studies are planned for 6 and 12 months after phase B through interviews investigating whether the possible effects of changing the healthcare environment are sustainable [33].

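### The one named numerical effect statistic takes no account of time order, so a steady drift can look like a ward effect or hide one; trend is handled only by eye

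*Protocol article*

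**What the plan says.** The Quantitative data part of the Analysis section announces visual and numerical methods and notes of this research tradition: "Thus, traditional inferential statistics are rarely used". Two tools are then named.

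- Visual: "Visual inspection of the data requires comparing levels, trends, and changes between intervention phases".
- Numerical, with the extreme taken from phase A: "Also, the percentage of non-overlapping data statistics will be calculated, i.e. the percentage of phase B data that overlaps with the most extreme data point".

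The input to both is the ward mean. For each questionnaire the data "will consist of the mean ratings from all participants, patients, and staff respectively, answering at each point in time".

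The Methods and Setting sections describe one ward that passes once from phase A to phase B and acts as its own control. Phase A runs on a temporary relocation ward, with "through outcomes measured twice a week for approximately 5 weeks". No cut-off is set for the percentage, and nothing is said about how to read it when phase A is already trending.

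**The concern.** The percentage depends only on the set of phase B means and on one extreme phase A mean. Shuffling the points within each phase leaves it unchanged. A scale that improves steadily from the first week, with nothing happening at the move, therefore places later points beyond the phase A extreme simply because they are later. A scale that is worsening does the opposite and can bury a real gain.

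Drift is plausible from the article itself. The same forms are completed repeatedly, phase A takes place on a temporary ward, and each mean comes from whoever answers that day, so the mix of respondents can shift. With one ward and no concurrent control, nothing else in the numbers would reveal it.

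The statistic serves both primary outcomes (CPS for patients, PSS for staff) and the other repeated scales (ORS, HAD, SCQ). Two stated purposes are affected: the research questions on whether the design influences these outcomes, and the feasibility objective on how well the questionnaires detect change.

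**Working it through.** The article states no value of the percentage, no drift, no SD and no error rate, so there is no figure of its own to reproduce.

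**Inputs from the article: number of occasions (A/B).**
- Table 1: 5/10, taken here as weekly.
- Procedure: 2 × 5 = 10 in phase A; weekly for 2 months, about 9, in phase B: 10/9.
- Questionnaires section, twice weekly in both phases: 10 in phase A and about 17 in phase B: 10/17.

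**Assumptions.** Ward mean = d × week + noise with SD 1; no effect at the move; no gap between phases. The statistic is read as true non-overlap: the share of phase B points above the phase A maximum, with improvement upward. The mark of more than half is illustrative only.

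**Step 1, exact cases.** With no drift and independent points, a given phase B point exceeds all nA phase A points with probability 1/(nA + 1): 1/6 = 16.7% for 5/10, and 1/11 = 9.1% for 10/9 and 10/17. With a steady favourable drift and no noise, the value is 100%.

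**Step 2, simulation with no ward effect** (40,000 series per setting, independent noise). Each cell gives mean non-overlap, then the chance that more than half of phase B is non-overlapping.

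| Drift, SD per week | 5/10 | 10/9 | 10/17 |
|---|---|---|---|
| 0 | 17%, 4% | 9%, 1% | 9%, 1% |
| 0.1 | 37%, 24% | 23%, 10% | 23%, 8% |
| 0.2 | 59%, 58% | 42%, 37% | 42%, 36% |
| 0.3 | 74%, 83% | 59%, 68% | 60%, 70% |
| 0.5 | 88%, 98% | 78%, 95% | 79%, 96% |

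Lag-1 correlation of 0.3 changes little (5/10 at 0.3 SD per week: mean 75%). A gap between phases makes it worse: for 5/10 at 0.2 SD per week the mean rises from 59% to 79% with 4 weeks and 92% with 8 weeks.

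**Step 3, a real gain against an opposing drift.** Here drift is counted per occasion and lag-1 correlation runs from 0 to 0.5. A true 2-SD improvement gives mean non-overlap of 65–80% with no drift, but 5–36% against an opposing drift of 0.2 SD per occasion.

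**Step 4, does adjusting for time separate the two?** A regression with a common slope and a step at the move gives a mean step within 0.01 SD of zero at every drift in step 2. It is not enough, however, if the benefit builds up. For a gain rising linearly to 2 SD across phase B with no drift, the common-slope step averages −0.24 SD (5/10) and −0.26 SD (10/17). A slope change is needed as well.

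**Step 5, price of the fuller model.** With separate lines in A and B, the level change at week 5 has variance (independent noise, SD 1)

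1/nA + (5 − mean tA)²/SxxA + 1/nB + (5 − mean tB)²/SxxB.

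- 5/10: 0.2 + 3²/10 + 0.1 + 4.5²/82.5 = 1.446, SE 1.20.
- 10/9: 0.1 + 2.75²/20.625 + 0.111 + 4²/60 = 0.844, SE 0.92.
- 10/17: 0.1 + 2.75²/20.625 + 0.059 + 4²/102 = 0.682, SE 0.83.

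With lag-1 correlation of 0.3 to 0.5 these become 1.0 to 1.3.

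**The case against.** The strongest reply is that trend is already in the plan. Visual analysis comes first and expressly covers trends; the percentage is added as a supplement. A steady line running through the move is what such a plot shows. At 0.2 SD per week the total drift over the study is 0.2 × 14 = 2.8 SD on the Table 1 schedule, which would be hard to miss. The article sets no cut-off or decision rule, so no false-positive rate can be attributed to it. The study is framed as feasibility work, and the Discussion claims only changes that might be related to the design. Formal inference is unusual in this tradition, and a condensed article may leave further analyses to a fuller document.

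Most of this stands, and it limits the point. A reader might infer that the plan ignores trend, or that it will credit drift to the new ward. The article supports neither: it compares trends by eye and never proposes to read the percentage alone.

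What the reply does not remove is that the article itself chooses and defines this statistic as the numerical result, and the statistic carries no information on trend. If plot and percentage disagree, no number is planned that could settle it. The research questions do ask whether the design influences outcomes.

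**Conclusion.** The point holds in a limited form. The only named numerical effect statistic is blind to time order, and in a single A-to-B design it can report mostly non-overlapping data with no ward effect, or conceal a real one. Visual inspection covers this only by eye.

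The size rests on assumed drift and SD. Up to about 0.1 SD of the ward mean per week the percentage usually stays below half; from about 0.2 (Table 1 schedule) or 0.3 (ten phase A points) it usually exceeds half. The conclusion does not depend on the sentence's wording, which describes overlap under the name of non-overlap: it remains when the statistic is defined correctly and in the right direction. This is a worthwhile, inexpensive improvement, not a fault that invalidates the plan.

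**What to change.** In the Quantitative data part of the Analysis section, keep the visual analysis and the non-overlap percentage, and add:

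1. For each repeated scale, patients and staff separately, a descriptive segmented regression of the ward mean on calendar time, with a level change and a slope change at the move and allowance for autocorrelation. Report both in scale points, with an interval labelled approximate.
2. A statement that where phase A shows a trend, the non-overlap percentage is not by itself evidence of a change at the move.

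The label matters because the series are short. In null simulations of the simpler common-slope step, a first-order autoregressive fit by restricted maximum likelihood rejected in 7–9% of runs at correlation 0 and 9–12% at 0.5, against a nominal 5%.

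Two shortcuts should be avoided. The common-slope model alone misreads a gradual gain (step 4). Accepting the percentage whenever a fitted step has the same sign filters little: with no effect and drift of 0.2 SD per occasion, 53–66% of series with at least half non-overlap would still pass.

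The cost is a few lines of text and one small regression per scale on data already collected. With a standard error of about 0.8–1.3 SD of the ward mean for the level change, claims will have to be more modest.

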#### Feasibility objectives

The feasibility objectives are to discern the following:The properties of the questionnaires regarding detection of change;Whether the chosen questionnaires are suitable for frequent measurements; andThe plausible recruitment rates for this study.

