##### Semi-structured interviews

Both patients and staff will be interviewed by the researchers in semi-structured interviews [50]. Patients will be interviewed individually while staff will participate in focus groups. During phase B, patients will be interviewed very near to their discharge from the ward, while the focus group interviews with staff will be conducted at the end of phase B. The participants will be asked to share their experiences of the ward environment and its impact on the quality of their interactions. Staff will also be asked about the ward environment’s impact on their daily work and perceived stress. Table 1 shows a flowsheet of the data collection.

**Table 1 Tab1:** Modified SPIRIT-figure showing intervention and data collection flowsheet

Intervention phase	A					B									
Measurement no.	1	2	3	4	5	6	7	8	9	10	11	12	13	14	15
Assessments, patients															
CPS	●	●	●	●	●	●	●	●	●	●	●	●	●	●	●
ORS	●	●	●	●	●	●	●	●	●	●	●	●	●	●	●
HAD	●	●	●	●	●	●	●	●	●	●	●	●	●	●	●
QPC-IP	●														●
Interviews												●	●	●	●
Activity monitor		●	●							●	●				
Assessments, staff															
PSS	●	●	●	●	●	●	●	●	●	●	●	●	●	●	●
SCQ	●	●	●	●	●	●	●	●	●	●	●	●	●	●	●
QPC-IPS	●														●
Interviews												●	●	●	●
Activity monitor		●	●							●	●				
Observations at ward										●	●	●	●	●	●

*●*Measurement performed, *CPS* Caring Professional Scale, *ORS* Outcome Rating Scale, *HAD* Hospital Anxiety and Depression Scale, *QPC-IP* Quality in Psychiatric Care–Inpatient, *PSS* Perceived Stress Scale, *SCQ* Stress of Conscience Scale, *QPC-IPS* Quality in Psychiatric Care–Inpatient Staff, Supplementary data from ward registers will be collected continuously

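### The only numerical effect statistic named, PND, judges each phase B ward mean against one phase A point; an all-pairs index and the mean difference should be reported beside it

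*Protocol article*

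**What the plan says.** The quantitative analysis section of the protocol article combines visual and numerical methods. On the visual side: "Visual inspection of the data requires comparing levels, trends, and changes between intervention phases". On the numerical side one statistic is named: "Also, the percentage of non-overlapping data statistics will be calculated", explained as "the percentage of phase B data that overlaps with the most extreme data point in phase A". The values that enter it are ward averages, one per measurement occasion: "Measurement data for each of the questionnaires will consist of the mean ratings from all participants, patients, and staff respectively, answering at each point in" (quote cut one word short). No test, error rate, effect size or PND cut-off is given, and the section remarks that conventional inference is seldom used in this tradition.

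Five questionnaires are repeated: CPS, ORS and HAD for patients, PSS and SCQ for staff. The first feasibility objective concerns "The properties of the questionnaires regarding detection of change".

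The number of points per phase is not settled. Table 1 ("Modified SPIRIT-figure showing intervention and data collection flowsheet") shows 5 measurements in phase A and 10 in phase B. The Procedure section has "outcomes measured twice a week for approximately 5 weeks" in phase A (about 10) and "outcomes will be measured once a week over a period of 2 months" in phase B (about 8 or 9). The Questionnaires section says twice weekly in both phases (about 16 in phase B).

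**The concern.** A ward mean is a continuous quantity, and PND keeps only whether each phase B mean lies beyond one cut. That cut is one phase A observation. The other baseline points (4 of 5 in Table 1, about 9 of 10 under the Procedure section) serve only to establish which point is the extreme one. How far the phases lie apart does not enter.

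Two consequences matter here. The cut moves outward as baseline points are added, so the same true change gives a lower percentage with a longer baseline, and the protocol's own schedules disagree on that length. A single odd phase A occasion also sets the cut. That is plausible on this ward, because the number of patients behind each mean depends on who is admitted that day.

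At stake is the one numerical summary planned for the primary outcomes (CPS and PSS) and for judging how well the questionnaires register change.

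**Working it through.** The plan gives no power, error rate, effect size or SD, so there is no figure of its own to reproduce. The check takes PND in its usual sense, the share of phase B points beyond the most extreme phase A point. That the quoted definition says overlap where the name says non-overlap is a separate matter of wording.

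**Inputs from the protocol article.** Phase lengths 5+10 (Table 1) and about 10+9 (Procedure).

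**Assumptions.** Normal ward means with occasion-to-occasion SD 1; a level shift of d SDs in phase B; lag-1 autocorrelation 0 or 0.3; improvement taken as upward; each statistic calibrated to a one-sided 5% false-positive rate, with randomisation at the boundary for discrete statistics.

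**Statistics.**
- PND = share of phase B points above the phase A maximum.
- NAP = share of all phase A × phase B pairs in which B exceeds A.
- Mean difference = mean of B minus mean of A.

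**Step 1: expected values, where no detection rule is needed.** With independent points, E(PND) = ∫ Φ(y)^nA φ(y − d) dy and E(NAP) = Φ(d/√2).
- d = 0: E(PND) = 1/(nA + 1), so 1/6 = 17% with 5 baseline points and 1/11 = 9% with 10. E(NAP) = 50% in both.
- d = 1: E(PND) = 45% with 5 points, 32% with 10. E(NAP) = Φ(0.707) = 76% in both.
- d = 1.5: E(PND) = 61% with 5 points, 49% with 10. E(NAP) = Φ(1.061) = 86% in both.

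**Step 2: one unusual baseline occasion.** Doubling the SD of one phase A point (5+10, d = 1.5) lowers expected PND from 61% to 53% and expected NAP from 86% to 83%. The chance that PND is 20% or less rises from 10% to 22%.

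**Step 3: detection under the assumed rule.** With no effect, P(at least k of 10 phase B points exceed the phase A maximum) = C(15 − k, 5)/C(15, 5). For k = 6 this is 126/3003 = 4.2%, and for k = 5 it is 252/3003 = 8.4%. The 5% rule is therefore 6 or more of 10, with randomisation at 5. Simulated detection rates (100,000 runs per setting; repeat runs differ by up to about one point):

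| Points A+B | Autocorrelation | d | PND | NAP | Mean difference |
|---|---|---|---|---|---|
| 5+10 | 0 | 0.5 | 17% | 21% | 23% |
| 5+10 | 0 | 1 | 39% | 51% | 57% |
| 5+10 | 0 | 1.5 | 64% | 80% | 86% |
| 5+10 | 0.3 | 0.5 | 15% | 16% | 18% |
| 5+10 | 0.3 | 1 | 33% | 38% | 42% |
| 5+10 | 0.3 | 1.5 | 56% | 64% | 70% |
| 10+9 | 0 | 1 | 42% | 65% | 70% |
| 10+9 | 0 | 1.5 | 68% | 92% | 95% |
| 10+9 | 0.3 | 1 | 37% | 48% | 52% |
| 10+9 | 0.3 | 1.5 | 61% | 77% | 82% |

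The mean-difference column treats the occasion SD as known. Hand check for 5+10, d = 1: Φ(1/√(1/5 + 1/10) − 1.645) = Φ(0.181) = 57%. Dividing by an SD pooled within both phases instead gives 53% (5+10) and 67% (10+9) at d = 1 with independent points.

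**Step 4: the ceiling.** PND is 100% exactly when every phase B point exceeds the phase A maximum, which is exactly when every pair favours phase B. At d = 3 with 5+10 points, both statistics are 100% in the same 65% of runs.

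**Step 5: ranking two questionnaires with true shifts of 1 and 1.5 SD (5+10, independent points).** PND orders them wrongly in 28% of runs and ties in 9%. The mean difference divided by the phase A SD is wrong in 31%. Divided by the pooled SD it is wrong in 28%, without ties. The phase A SD has 4 degrees of freedom, so its 95% interval runs from about 0.6 to 2.9 times the estimate. The pooled SD has 13, with an interval of about 0.7 to 1.6 times.

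**The case against.** The strongest reply is that no detection rule exists here to be weak. The plan is descriptive, and any power figure belongs to a test that it does not propose. This stands: the rates in step 3 hold only under the assumed rule. Steps 1 and 2 need no such rule.

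Second, visual inspection of level and trend uses every baseline point and shows the distance between phases, so an odd phase A occasion would be seen. This also stands. PND is the only numerical statistic named, not the only analysis. A reader might infer that the study will miss real changes or discard a usable questionnaire because of PND; the protocol article contains no decision rule driven by PND, so that does not follow. What visual inspection lacks is a stated quantity by which to compare five questionnaires.

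Third, an all-pairs index shares some of PND's limits. It is rank-based, so it carries no magnitude, and it reaches its ceiling in the same runs. A reader might infer that NAP removes the 100% ceiling; step 4 shows that it does not. Nor does dividing the difference by the phase A SD give a better ranking of questionnaires than PND when there are 5 baseline points.

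Fourth, successive ward means share staff and overlapping inpatients, so independence is optimistic. For 5+10 points, NAP's gain at autocorrelation 0.3 is about 1 to 8 points. Finally, PND is established in this design tradition, which is a reason to keep it but not to report it alone.

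**Conclusion.** The point holds as an inexpensive improvement to the analysis, not as an error that invalidates it. PND makes poor use of continuous ward means: it omits distance, hangs on one baseline value and changes with baseline length (61% against 49% for the same 1.5 SD shift, where NAP stays at 86%).

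The loss in sensitivity is conditional. With independent normal ward means and an assumed one-sided 5% rule, NAP gains about 12 to 16 points over PND for shifts of 1 to 1.5 SD in the Table 1 layout, and about 23 to 24 points with 10+9. In the Table 1 layout it gains about 4 points at 0.5 SD, and about 5 points (1 SD) and 8 points (1.5 SD) with autocorrelation 0.3. A flat statement that real changes will be detected clearly less often goes further than the document allows, since shift, SD, autocorrelation and rule are all assumed. Of the three statistics only the mean difference carries magnitude, and none of them corrects for a baseline trend.

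**What to change.** In the quantitative analysis section, keep visual inspection and PND. Add for each of CPS, ORS, HAD, PSS and SCQ:

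1. NAP: the share of all phase A × phase B pairs in which the phase B ward mean lies in the improved direction for that questionnaire, ties counted half, with 50% meaning no change.
2. The phase B minus phase A difference in mean level, in scale points, shown with the occasion-to-occasion SD.

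Do not present NAP as free of the 100% ceiling. Do not rank questionnaires by the difference divided by the phase A SD alone. If a standardised figure is wanted for the first feasibility objective, divide by the SD pooled within both phases and describe the result as imprecise.

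The cost is about two sentences and a few lines of code on ward means already planned, with no new data or participants. The downside is two more descriptive figures per questionnaire to report and explain.

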## Methods

This is an intervention project using a single-system experimental design (SSED) with baseline and intervention phases [32]. SSED studies focus primarily on changes in one system (in this case the ward), and the system works as its own control. As single-system designs aim to detect changes within each system rather than to compare systems, sample sizes in this tradition are relatively small and no sample size calculations are made [33]. Data for the system will consist of aggregated measurements from patients and staff respectively on the ward [32, 33]. This means that the total number of individuals included in the study depends on (a) the number of patients admitted to the ward at each point of measurement and (b) the number of staff members working on the ward. In parallel, a process evaluation is performed to describe patient experiences and important contextual factors.

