#### Questionnaires

During both phases, measurements will be taken twice a week, with an assigned staff member distributing the questionnaires to the participants. Based on results from previous research [12, 34] showing that experiences of interactions with staff are related to experiences of the physical environment, the primary outcome measure for patients will be the perceived quality of their interaction with the staff. Secondary outcome measures will be levels of depressive symptoms, anxiety, satisfaction, and quality of care.

Based on results from previous research [13, 35, 36] showing that staff in psychiatric inpatient care experience stress related to inadequate physical environments, the primary outcome measure for staff will be perceived stress. Secondary outcome measures will be stress of conscience and quality of care. Demographic data will be collected for all participants.

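### The percentage of non-overlapping data is defined as its complement, so the only numerical effect statistic named would run backwards if the definition were followed

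*Protocol article*

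**What the plan says.** The Quantitative data section of the protocol article plans visual inspection of levels, trends and changes between phases, and then adds a number: "the percentage of non-overlapping data statistics will be calculated". The same sentence explains this number as "the percentage of phase B data that overlaps with the most extreme data point in phase A".

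The data points are ward-level averages, with patients and staff analysed separately: "Measurement data for each of the questionnaires will consist of the mean ratings from all participants".

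The article remarks that traditional inferential statistics are rarely used in this research tradition, and under Methods it says that "no sample size calculations are made". It names no model, test, interval or other numerical effect measure.

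**The concern.** Overlap and non-overlap are complements: a phase B point either lies beyond the most extreme phase A point or it does not. The name of the statistic and its explanation therefore cannot both be followed. The explanation is the only operational rule given.

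Under the named statistic, a high value means that the phases separate. Under the written rule, a high value means that they do not. An analyst who follows the explanation and reports under the name would present absence of change as strong change, and the reverse. This would reach both primary outcomes: quality of interaction (CPS) for patients and perceived stress (PSS) for staff. It also bears on the first feasibility objective, which concerns how well the questionnaires detect change, because a reversed statistic would rank the instruments in the wrong order.

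**Working it through.** The plan states no PND value, so there is no figure to reproduce. The check is what each reading returns in known situations.

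**Inputs**
- Phase A points, nA: about 10 from Procedure ("through outcomes measured twice a week for approximately 5 weeks", so 2 × 5), but 5 in Table 1 (measurements 1 to 5). Both are used.
- Phase B points: 10 in Table 1 (measurements 6 to 15); about 8 to 9 from Procedure ("outcomes will be measured once a week over a period of 2 months"); about 16 to 18 from Questionnaires ("During both phases, measurements will be taken twice a week"). The expected values below do not depend on this number.

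**Complete separation.** Every phase B point lies beyond every phase A point. PND = 100%. Written rule = 100% − 100% = 0%.

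**No effect.** Assume that the nA phase A points and any one phase B point are exchangeable and untied, and that the comparison is one-sided. The phase B point is then the most extreme of nA + 1 points with probability 1/(nA + 1). So:
- expected PND = 1/(nA + 1)
- expected value of the written rule = nA/(nA + 1)

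| | nA = 5 | nA = 10 |
|---|---|---|
| PND, no effect | 1/6 = 16.7% | 1/11 = 9.1% |
| Written rule, no effect | 5/6 = 83.3% | 10/11 = 90.9% |

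**Simulation** (100,000 independent normal series per setting, 10 phase B points), mean value of the written rule:

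| Shift in phase B | nA = 5 | nA = 10 |
|---|---|---|
| 0 SD | 83.4% | 90.9% |
| 1 SD | 55.1% | 67.7% |
| 2 SD | 24.3% | 34.3% |
| 6 SD | 0.0% | 0.0% |

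The written rule falls as the effect grows. PND is 100% minus each entry.

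**Sensitivity of the no-effect value of the written rule**
- Serial dependence, AR(1) with correlation 0.3 and 0.6, 10 phase B points: 80.7% and 76.2% for nA = 5; 89.4% and 86.0% for nA = 10.
- Overlap read as lying anywhere within the phase A range: (nA − 1)/(nA + 1), which is 4/6 = 66.7% for nA = 5 and 9/11 = 81.8% for nA = 10.

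The level moves with the assumptions. The reversal does not.

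**QPC-IP and QPC-IPS.** Table 1 schedules these only at measurements 1 and 15, one point in each phase. With a single phase B point, PND can only be 0% or 100%, and with nA = 1 its chance value is 1/(1 + 1) = 50%. It carries no useful information for these two scales.

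**The case against.** The strongest reply is that this is a slip of wording. The statistic is named correctly and a methods reference is cited for it, so an analyst who computes what is named gets the right number. This is plausible, and it lowers the severity. It does not remove the contradiction, because the explanation is the only rule on the page and readers will check the results against it.

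A reader might infer more than the article supports, in four ways.

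- *That the trial's results will be reported backwards.* The article cannot show which half of the sentence the analyst will follow.
- *That the effect analysis rests on this number alone.* It does not. Visual inspection comes first and PND is added to it, so a reversed percentage would sit beside a plot that contradicts it. No threshold or success rule depends on PND, and the stated focus of this study is feasibility.
- *That 83% to 91% is what no effect must give.* The range needs exchangeable, untied points and a one-sided comparison. Repeated ward means, partly from the same staff, may well be serially dependent.
- *That the missing direction for each scale is a separate error.* The article gives only item counts and response formats for CPS, PSS and HAD, and an article may leave scoring to a fuller document. Direction matters here only because a corrected definition cannot be applied without it.

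**Conclusion.** The contradiction is certain and lies within one sentence: the percentage of non-overlapping data is defined as the percentage that overlaps. If the definition is followed, the only numerical effect statistic named runs backwards for every repeatedly measured scale. With complete separation the error is the full range, 0% in place of 100%, and this needs no distributional assumption. The no-effect figures (about 83% or 91% in place of about 17% or 9%) are illustrations under the assumptions stated with the calculation, and the two values reflect the two baseline lengths in the article.

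This should be fixed. It is not a fatal flaw: the name is right, visual inspection stands beside the number, and no decision rule hangs on it.

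**What to change.** Replace the definition with: the percentage of phase B data points that lie beyond the most extreme phase A data point in the direction of improvement.

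State that direction for each repeatedly measured scale (CPS, ORS, HAD, PSS, SCQ) according to its scoring. Say that the statistic is not applied to QPC-IP or QPC-IPS.

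The cost is a sentence or two in the analysis section. Data collection does not change and no further statistic is needed. Reporting the chance value 1/(nA + 1) beside each PND would help readers, but it is optional and not part of the correction.
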